### 3.9.2. Additional analyses

N/A

### 3.9.3. Analysis population and missing data

N/A

## 3.10. Data monitoring

### 3.10.1. Formal committee

As this is a single institute observational study, we did not plan to set Data Monitoring Committee, DMC.

### 3.10.2. Interim analysis

N/A

## 3.11. Safety/harms

As our study is observational study with questionnaire, we don’t have therapeutical interventions, therefore we do not assume harms nor adverse event. However, during completing our questionnaire with ePRO, the participant will have potential to face difficulty of mental uncomfortableness. In such cases we would immediately consult our psycho-oncology teams.

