## 3.4. Outcomes

Primary outcome:

Depression

The nine items of Patient Health Questionnaire-9 (PHQ-9) [Spitzer et al., 1999] will be used to measure depression. Higher scores indicate greater possibility of major depression (a PHQ-9 score ≥10, the cut off score, had a sensitivity of 88% and a specificity of 88% for major depression).

Secondary outcomes:

Anxiety

The seven items of General Anxiety Disorder-7 (GAD-7) [Spitzer et al., 2006] will be used to measure anxiety. Higher scores indicate greater possibility of generalized anxiety disorder (a GAD-7 score ≥10 had a sensitivity of 89% and specificity of 82% for generalized anxiety disorder).

QOL

The 30 items of the European Organization for Research and Treatment of Cancer Quality of Life Questionnaire module Core 30 (EORTC QLQ−C30) [Aaronson et al., 1993] will be used to measure QOL. For global QOL scale and functional scales, higher score indicates a better level of function. For symptom-oriented scales, higher scores indicate more severe symptoms.

Symptoms

The nine items of the Edmonton Symptom Assessment System (ESAS) [Yokomichi et al., 2015] will be used to measure symptoms. High scores indicate greater morbidity.

Qualitative interviews

All participants with a PHQ-9 score above cut-off, and a small convenience-selected subset of participants will be invited at baseline and at each follow-up time-point to participate in structured interviews based on SCID-IV [JAMA, 2015].

Knowledge

A 10-item, multiple choice, study-developed questionnaire will be used to assess knowledge of the purpose of CGP testing, likely frequency of informative results, cancers in which informative results are more likely to be found, availability of tailored treatment options, and source of genetic knowledge. Scores will be summed from 0 to 10, with high scores indicating greater knowledge.

Satisfaction

The five items of the Patient Satisfaction Questionnaire (PSQ) will be used to measure satisfaction. Lower scores indicate higher satisfaction. [Blanchard et al., 1986]

Quality of communication

The 11 items on the quality of communication in the Health Information National Trends Survey (HINTS) will be used to measure quality of communication. High scores indicate greater communication.  [Smith et al., 2015]

Social support

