## 3.8. Data management

Participants will be asked to complete a questionnaire using an electronic patient reported outcome (ePRO) application software or hard copy at baseline (T0), 1 to 4 weeks after receiving the results of CGP testing (T1; approximately 2–3 months post baseline), 3 months (T2) after T1, and 6 months (T3) after T1. These timeframes have been chosen to allow the impact of the test results to be captured in both the short term (when a treatment decision is being made) and longer term (while undergoing or close to completion of the targeted therapy, if adopted). All patients with a PHQ-9 score at the cutoff point of 10 or above (total score) as well as a small subset of participants (around 20–40) selected as a convenience sample who score below this cutoff point will be interviewed using the Structured Clinical Interview for DSM-V-RV (SCID), which includes items on mood disorders, neurotic, stress-related and somatoform disorders, and behavioral syndromes associated with physiological disturbances and physical factors, at each assessment time-point to determine the 4-week and lifetime prevalence rates of comorbid mental disorders

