## 4.7. Ancillary and post-trial care

Information related to this research will be stored in accordance with the Standard Operating Procedures: SOP established by the institute. Information and research materials shall be preserved for 10 years from the publication of the study papers.

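### Sections 3.4 and 3.8 disagree on whether high-scoring family members get the SCID, and the consultation trigger in 3.11 leaves out the interview and paper completion

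*Protocol*

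**What the plan says.** **Who is interviewed.** Section 3.4 (Outcomes) states: "All participants with a PHQ-9 score above cut-off, and a small convenience-selected subset of participants will be invited". Section 3.7.2 uses participants for patients and family members alike. Section 3.8 (Data management) instead states "All patients with a PHQ-9 score at the cutoff point of 10 or above (total score", and adds about 20 to 40 participants "selected as a convenience sample who score below this cutoff point". Both sections place the interview at every assessment time-point. The only purpose that 3.8 gives for it is to establish how common mental disorders are, over four weeks and over a lifetime.

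**Safety response.** Section 3.11 does not expect harms, and its reason begins "As our study is observational study with questionnaire". It then allows for one exception, "during completing our questionnaire with ePRO, the participant will have potential to face difficulty of mental uncomfortableness", and gives the response: "In such cases we would immediately consult our psycho-oncology teams". Section 3.8 lets participants use paper instead of the electronic form.

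**Other places to look.** Section 4.7 is headed as covering ancillary and post-trial care. It opens "Information related to this research will be stored in accordance with the Standard Operating Procedures: SOP established by the institute" and then gives a retention period. Section 3.7.2 lets the investigator withdraw a participant for safety. Section 6.1 refers to a separate consent document, which is not among the documents at hand.

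**The concern.** The interview rule is stated twice, with different populations. Section 2.2 aims at patients and family members, and section 3.9.1 plans to report other mental comorbidity as a raw rate in the total sample. If 3.8 governs, the family members most likely to have a disorder are not interviewed, while some of those least likely to have one may be. The family figure would then reflect the selection rule more than the population.

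The safety section describes a narrower study than the one planned. The study makes psychiatric diagnoses at each time-point, yet the written consultation trigger concerns discomfort with an electronic questionnaire. A site following the text has a named team but no written instruction for a participant whose interview shows a current disorder, or who becomes distressed during that interview.

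**Working it through.** **1. The plan's figures.** Section 3.6: 33 × 12 = 396 patients tested per year; 396 × 0.75 = 297, planned as 300. Family members: 300 × 0.80 × 0.80 = 192, planned as 200. Family share of planned enrolment: 200 / (300 + 200) = 40%.

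**2. The two interview rules side by side.**

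| Person and score | Section 3.4 | Section 3.8, read literally |
| --- | --- | --- |
| Patient, 10 or above | invited | interviewed |
| Patient, below 10 | possible (subset) | possible (subset) |
| Family member, 10 or above | invited | not named |
| Family member, below 10 | possible (subset) | possible (subset) |

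The rules differ in one cell: the high-scoring family member. Section 3.4 defines its own cutoff as 10 or more, so the difference in how the two sections word the cutoff is trivial.

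**3. What that cell does to the family estimate.** Section 3.4 says that a PHQ-9 of 10 or more "had a sensitivity of 88% and a specificity of 88% for major depression". The protocol gives no expected prevalence, so I assume p = 5%, 10% or 20%. Per 100 family members at one time-point:

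- Cases at or above the cutoff = 100 × 0.88 × p = 4.4, 8.8, 17.6.
- Cases below it = 100 × 0.12 × p = 0.6, 1.2, 2.4.
- Non-cases below it = 100 × 0.88 × (1 − p) = 83.6, 79.2, 70.4.
- Rate among low scorers = 0.6/84.2, 1.2/80.4, 2.4/72.8 = 0.7%, 1.5%, 3.3%.

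Interviewing only low scorers would therefore show about 0.7%, 1.5% or 3.3% where the truth is 5%, 10% or 20%. This treats the subset as random among low scorers, which a convenience sample need not be, and it covers major depression only.

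**4. What 3.11 names, against what the study does.** Electronic questionnaire: named. Paper questionnaire (3.8): not named. SCID interview (3.4, 3.8): not named. Current disorder found at the SCID: not named. Score of 10 or more with the invitation declined (3.4): not named. No other visible section supplies a care step: 3.7.2 gives withdrawal, 4.7 gives storage, and 6.1 describes voluntariness and privacy.

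**5. Workload of the fix, per 100 assessments.** Screen-positives = 100 × 0.88 × p + 100 × 0.12 × (1 − p) = 15.8, 19.6, 27.2. Let a be interview uptake, assumed unrelated to true status, and take the SCID as correct for major depression. If every decliner who is told about consultation also takes it up, consultations = a × true positives + (1 − a) × screen-positives:

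- a = 1: 4.4, 8.8, 17.6.
- a = 0.75: 7.3, 11.5, 20.0, of which 2.9, 2.7 and 2.4 are false positives.
- a = 0.5: 10.1, 14.2, 22.4, of which 5.7, 5.4 and 4.8 are false positives.

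The specificity may not hold in this population. Screen-positives would be 28.2, 31.3, 37.6 at 75% specificity and 9.2, 13.3, 21.6 at 95%. Other SCID disorders would add to the consultations.

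**The case against.** The safety part is largely an omission, and the likeliest home for a referral step is the consent document, which cannot be checked here. Section 3.11 forbids nothing. Its English is loose, so taking the electronic form as a deliberate exclusion of paper, or the questionnaire as a deliberate exclusion of the interview, may read too much into it. A high score is not ignored either: it leads to a diagnostic interview by people who may well refer. All of this stands, and it limits the safety part to a clarification.

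On family members, nothing says that 3.8 overrides 3.4, so the site may already be inviting them. That also stands. But two rules for one procedure cannot both be followed, and one of them defeats a stated aim.

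Three stronger readings are tempting and not supported:

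- That care is confined to distress during the electronic questionnaire. The text names that case; it does not say other cases are refused.
- That high-scoring family members get neither interview nor care, or that 40% of participants are affected. The first requires 3.8 to prevail and clinicians to do nothing. The 40% is only the family share of planned enrolment.
- That the per-100 figures count people left without care. They show screening yield and workload under assumed prevalence.

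**Conclusion.** The contradiction between 3.4 and 3.8 is established from the text and should be resolved. Its effect depends on which rule is followed. Under 3.8, SCID-based comorbidity in family members cannot be validly estimated, and in the illustration the low scorers show a rate roughly one-seventh to one-sixth of the true one (0.7/5 to 3.3/20). That size rests on the cited accuracy holding here and on assumed prevalence. The PHQ-9 depression prevalence, the primary outcome, is not affected by this conflict.

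The 3.11 trigger is narrower than the study it covers and should be extended. This holds with moderate confidence, because the consent document may already contain the missing step.

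**What to change.** - **Section 3.8:** replace patients by participants (patients and family members) with PHQ-9 of 10 or more, which is what 3.4 already plans. This removes the exclusion. The low scorers remain a convenience sample, which is a separate limit on any comorbidity estimate.
- **Section 3.11:** describe the study as including diagnostic interviews. Offer psycho-oncology consultation to any participant with a SCID-diagnosed current (4-week) disorder, or with distress during the interview or paper completion. Tell those scoring 10 or more who decline the interview that consultation is available. If the consent document already provides this, 3.11 need only cite it.
- **Data:** record each referral with its date and report referrals beside the T1 to T3 prevalence.

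The cost is a short amendment and one recorded item; the score and the team already exist. Extra consultations should be modest, as in step 5, and informing decliners instead of referring them leaves the choice with people who have already declined further contact. Referral may slightly lower depression at T1 to T3, so later prevalence must be read as prevalence with referral in place. Assessments before and after the amendment would be made under different rules. Section 1 lists recruitment as ongoing, but the number of assessments still to come is not given, and the change reaches only those.

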# 4. ETHICS AND DISSEMINATION

## 4.1. Research ethics approval

This study has been approved by the National Cancer Center Institutional Review Board (2019-315). The results will be published in a scientific peer-reviewed journal, and findings will be disseminated at the domestic and international levels.

## 4.2. Protocol amendments

## 4.3. Informed consent process

Patients will provide consent for the study to Q-CAT staff at the same time they give consent to the CGP or within one week thereafter. Thus, at baseline they will have already considered and given consent for CGP testing but will not have received the results of CGP testing. Participants will be asked to complete a questionnaire using an electronic patient reported outcome (ePRO) application software or hard copy at baseline (T0), 1 to 4 weeks after receiving the results of CGP testing (T1; approximately 2–3 months post baseline), 3 months (T2) after T1, and 6 months (T3) after T1. These timeframes have been chosen to allow the impact of the test results to be captured in both the short term (when a treatment decision is being made) and longer term (while undergoing or close to completion of the targeted therapy, if adopted).

### 4.3.1. Ancillary studies

N/A

## 4.4. Confidentiality

Study participant will be anonymized with a research number. Research number and personal identification information are only connected by correspondence table, and the table is managed by personal information manager. Only anonymized data will be collected and be used in this study. All data are symbolized, digitized and stored primary in a secure external database and finally in the center. Personal information manager manage data in personal computer isolated from outside, take safety measures against information leaks by storing computers in a high-security room. In addition, the results of the research will not be reported or published in a manner that identifies individuals.

## 4.6. Access to data

Study participant will be anonymized with a research number. Research number and personal identification information are only connected by correspondence table, and the table is managed by personal information manager. Only anonymized data will be collected and be used in this study. All data are symbolized, digitized and stored primary in a secure external database and finally in the center. Personal information manager manage data in personal computer isolated from outside, take safety measures against information leaks by storing computers in a high-security room. In addition, the results of the research will not be reported or published in a manner that identifies individuals.

## 4.7. Ancillary and post-trial care

Information related to this research will be stored in accordance with the Standard Operating Procedures: SOP established by the institute. Information and research materials shall be preserved for 10 years from the publication of the study papers.

## 5.2. Funders

This work is supported by Japan Society for the Promotion of Science (JSPS) grant number 20K21742 and Daiwa Securities Health Foundation.

# 6. APPENDICES

## 6.1. Informed consent materials

This study is observational study and possesses no interventions. We also don’t use any human biological specimens. However, as we handle special care-required personal information, we obtain consent using the written document from participants.

The consent document outlining this research will be used to explain this study, and appropriate written consent will be obtained from the patient and their family members. Participation in this research shall be of the individual’s own free will, and it shall be explained in writing that even after consenting to this research, the individual may withdraw at any time, and that there will be no disadvantages due to non-participation or withdrawal. Also, explain in writing that the results obtained will be processed statistically and that personal privacy will be strictly protected. In addition. Once participants are enrolled, they will not be de-registered (deleted from the database) unless there is a withdrawal of consent, including a refusal to use the data for research purposes.

## 6.2. Biological specimens

## N/A
